## **Research Synopsis**

**Study Title:** Can immersive virtual reality magnify treatment outcomes of script training on Cantonese speakers with chronic aphasia? A randomized controlled trial

## **Study Population**

Cantonese-speaking individuals with post-stroke aphasia

## **Study Design**

A prospective, three-armed, open-label, assessor-blinded RCT will be conducted over a period of 20 weeks, based on a treatment protocol developed by the project team (Wong & Li, submitted). Protocol design and data reporting are aligned with the Consolidated Standards of Reporting Trials Statement (CONSORT) for nonpharmacologic trials (Boutron et al., 2017).

Trial Registration Data Set has been registered in ClinicalTrials.gov (NCT06722092).

## **Sample Size/inclusion/exclusion criteria**

A total of 105 Cantonese PWA will be recruited from rehabilitation centers/support groups for stroke patients in Hong Kong, and the speech therapy clinics of the local institute. Sample size is based on a power analysis of 90% with  $\alpha=.05$ , a medium effect size (which is considered conservative with respect to previous studies with comparable total time for treatment such as Cherney et al., [2014] and our pilot study (Wong et al., submitted), in which a large effect size was obtained), and an estimated attrition rate of 15%. Inclusion criteria include: 1) a stroke onset of more than six months, with an Aphasia Quotient (AQ) below 96.4, as evaluated by the Cantonese version of Western Aphasia Battery (CAB; Yiu, 1992), 2) premorbid fluent Cantonese speakers, 3) aged between 30 and 80 years, 4) no reported progressive neurogenic disorders such as dementia or Parkinson's disease, 5) no motor speech disorders of moderate to severe level, and 6) normal or corrected-to-normal vision and hearing functions. (R6) Recruitment through the collaborating rehabilitation centers and support groups for PWA will be done via posters and social media posts. Screening will be done by a trained research postgraduate student/research assistant with speech therapy background.

## **Study Duration**

36 Months

### **Computerized script training**

A computerized script training program delivered in Cantonese, with procedures adopted from Cherney et al. (2008), will be used. The program has already been developed by the PI as supported by an internal grant provided by the institute (R2). Each treatment session begins with a session probe, which monitors the PWA's performance on scripts trained in previous sessions without support/cueing. If the performance on a certain script exceeds 90% in consecutive two sessions, a new script will be introduced. Treatment follows the sequence of: 1) The whole conversation script will be presented on a computer screen and read aloud by the virtual clinician, 2) The PWA will read each conversational turn assigned twice in unison with the virtual therapist. 3) The PWA will read aloud the sentence independently while the verbal response will be recorded by the program, 4) Treatment proceeds to another conversational turn. Each script will be repeated twice while two to three scripts will be trained in each session in random order. A clinical assistant will be present to monitor and provide technical support. Following computerized script training, the same sets of scripts will subsequently be practiced for 30 minutes, either in the VR or non-VR condition. The same set of procedures will be applied in the two treatment conditions; they only differ in terms of how treatment materials are presented.

### **VR treatment**

The PWA will wear an HMD (e.g., Oculus Quest 2) for 30 minutes. Interactive 360-degree videos depicting various daily scenarios will be presented. (R2) The immersive experience provided by the 360-degree videos will include a visual exploration of the scenario/surroundings (e.g., walking around in a fashion shop/reading a food menu in a restaurant) and audio input via stereo speakers provided by the HMD (traffic on the street, background noise of a Chinese restaurant, etc.). Interactive components will be achieved mainly via communication with the virtual communication partner and the subsequent event taking place. For example, a waiter in the restaurant will initiate a conversation (see Figure 2b). The PWA will be given time to respond. If a correct response is produced, the virtual communication partner will 'interact' with the PWA by initiating the next conversational turn, and, if applicable, nonverbal reactions/rewards such as presenting the object requested to the PWA. For incomplete or erroneous productions, PWA will be required to repeat the correct response in unison with the recorded model. The clinical assistant, who accompanies the PWA in the entire training session, will decide and control the type of feedback. Rests within

the session will be given and any possible adverse effects will be monitored and reported.

### **Non-VR treatment**

The flow of training is identical to the VR condition, except that only static photos depicting the scenarios and pre-recorded conversational turns will be presented to the PWA on a computer screen (Figure. 2c).

### **Research Questions**

1. Can script training promote verbal functional communication of Cantonese-speaking PWA?  
With regard to the evidence established in English speakers with aphasia and our pilot study, our proposed RCT can provide empirical evidence for the intervention approach.
2. Can script training enhance nonverbal cognitive functions of Cantonese-speaking PWA?
3. Can VR magnify verbal and nonverbal treatment outcomes of script training of PWA?

### **Primary Objective**

PWA's accuracy and time needed to produce the trained scripts (i.e., treatment probe) in read-aloud and no-cue conditions will be recorded via the computerized script training program. Similar to training, the virtual therapist will initiate the conversation, followed by PWA's response. The no-cue condition will be executed first, followed by the read-aloud condition. The performance of PWA receiving treatment on the session probe in terms of the number of sessions required to reach the performance criterion (i.e., 90% accuracy in consecutive two sessions) will also be considered.

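### Sessions-to-criterion, listed under the Primary Objective, comes from a probe run inside open-label treatment sessions, and the protocol does not show that its assessor blinding covers that probe

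*Protocol*

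**What the plan says.** - **Study Design** describes the whole trial in one label: "A prospective, three-armed, open-label, assessor-blinded RCT will be conducted".
- **Primary Objective** starts with accuracy and production time on the trained scripts. It then adds, for participants receiving treatment, that "the number of sessions required to reach the performance criterion (i.e., 90% accuracy in consecutive two sessions) will also be considered".
- **Computerized script training** places the measurement inside treatment: "Each treatment session begins with a session probe, which monitors the PWA's performance on scripts trained in previous sessions without support/cueing". The result also steers treatment: "If the performance on a certain script exceeds 90% in consecutive two sessions, a new script will be introduced". On staffing it says: "A clinical assistant will be present to monitor and provide technical support".
- **VR treatment** says of the same person: "The clinical assistant, who accompanies the PWA in the entire training session, will decide and control the type of feedback". **Non-VR treatment** describes the same flow with different presentation.
- **Statistical Analysis Plan** (a section of the protocol) has assessments administered by a research postgraduate student or by speech therapy students, and refers to blinding to condition. It gives scoring to the research postgraduate student in a general sentence. For the NORLA-6 scale it names the treatment and generalization probes. It does not mention the session probe.

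**The concern.** The session probe has two jobs. It decides when a new script is introduced, and it supplies an outcome placed under the Primary Objective. The no-treatment arm has no sessions, so the only randomized comparison this outcome can support is VR against non-VR, which is the third research question and the question in the title.

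The measure is a threshold count, so a few borderline responses credited or refused can move it by a session or more. If the person judging them knows the arm, leniency in one arm looks the same as faster learning. The assessor-blinded label would lead a reader to think this has been excluded, and the protocol does not say how.

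**Working it through.** **1. The sections side by side.** The protocol states no figure on this point, so the main check is textual.

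| Question | Treatment and generalization probes | Session probe |
|---|---|---|
| When given | Scheduled assessment timepoints | Start of each treatment session |
| Who is present or administers | Assessment staff, described as blinded | Only the clinical assistant is named, who knows the arm |
| Scoring scale | Adapted NORLA-6 | Not stated |
| Scorer | Research postgraduate student | Not stated, unless the general scoring sentence is meant to include it |
| Recording | Program recording stated for the treatment probe | Not stated (stated only for independent reading during training) |

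**2. Two possible readings of who scores.**

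- *The assistant scores.* The scorer knows the arm, and the label is wrong for this measure.
- *The postgraduate student scores.* Only treated participants have session probes. Linking a probe to a participant tells the student who is treated. The same student scores the other outcomes and may administer them, so blinding is weakened for the comparisons with no treatment.

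Neither reading, as written, secures masked assessment.

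**3. Illustrative size.** Assume one script, a constant pass probability *p* at each probe, and independent probes. There are 14 sessions and the probe covers scripts trained in earlier sessions, so a script trained from session 1 has at most 14 − 1 = 13 probes.

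Without a cap, the expected number of probes to two consecutive passes is (1 + p)/p²:
- p = 0.50: 1.50/0.25 = 6.00
- p = 0.60: 1.60/0.36 = 4.44

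With the cap, let a(k) be the probability that criterion has not been met after k probes. Then a(0) = a(1) = 1 and a(k) = (1 − p)·a(k−1) + p(1 − p)·a(k−2). The expected number of probes taken is a(0) + a(1) + … + a(12).

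| Assumed p, stricter arm | Assumed p, more lenient arm | Expected probes (stricter, more lenient) | Gap |
|---|---|---|---|
| 0.30 | 0.40 | 9.06, 7.21 | 1.86 |
| 0.50 | 0.60 | 5.61, 4.37 | 1.24 |
| 0.70 | 0.80 | 3.46, 2.81 | 0.65 |

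(Gaps are taken before rounding.) The uncapped gap at 0.50 against 0.60, 6.00 − 4.44 = 1.56, overstates the effect; 1.24 is the figure to use.

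**4. Threshold.** Computerized script training requires performance strictly above 90%. Primary Objective gives the criterion as 90% accuracy. A score of exactly 90% fails under the first and may pass under the second.

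**The case against.** A reader might infer that the assistant scores the probe live and that the measure is therefore not blinded. The documents do not go that far. During script training the assistant's stated tasks are monitoring and technical support. The control of feedback belongs to the later practice part, which is a different task from the uncued probe. The general sentence gives scoring to the postgraduate student, who on a natural reading is among the blinded staff. With sessions two or three times a week, and two consecutive sessions needed before a new script is added, scoring between sessions from recordings would be feasible. All of this stands, so the point is that blinding is not shown, not that it is absent.

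It does not rescue the label. Scoring between sessions needs a recording, and none is stated for this probe. Scoring by the postgraduate student creates the second problem in the working. Whoever scores it, no blinded administration is provided inside a treatment session.

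It is also fair that the measure is supplementary, that no VR versus non-VR test of it is written down, and that the pass probabilities, the absence of learning and the direction of bias have no source in the protocol. These limit the weight of the point. They do not remove it: the measure sits under the Primary Objective, and the only arms that have it are those two.

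Details of scoring can be left to a separate analysis plan. The blinding label is different, because the protocol itself makes that claim for the trial as a whole.

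**Conclusion.** The point holds in this limited form: the assessor-blinded label is not shown to cover sessions-to-criterion, a measure listed under the Primary Objective. If the general scoring sentence is meant to cover it, blinding of the other outcomes against the no-treatment arm is weakened instead.

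The size is illustrative only. A ten-point difference in pass probability gives a spurious gap of about 1.2 probes at 0.50 against 0.60, and between about 0.7 and 1.9 over the range shown. This assumes one script, constant and independent pass probabilities and a cap of 13 probes. The gap would favour whichever arm is scored more leniently; nothing in the protocol shows that this would be VR.

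The two threshold wordings are a separate, smaller inconsistency. They say nothing about blinding, but they leave the outcome without a single definition. The matter should be settled before the measure is used to compare the arms. It does not touch the definition of the main accuracy and time outcomes.

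**What to change.** **Option A: keep the outcome and mask it.**
- Use the running score only for script progression.
- State that session probes are recorded, and derive sessions-to-criterion from those recordings, scored with arm and identity masked.
- Score them after the other outcomes have been scored, so that handling session probes cannot reveal who was treated.
- Name the scorer and the scoring rule. The probe comes before the arm-specific practice, so its recording need not reveal VR or non-VR.

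Cost: 105 × 2/3 = 70 treated participants × 13 sessions = up to about 910 probe sessions, before attrition. Performance is judged per script, so the count of scores is higher. If two to three scripts are probed each time (an assumption carried over from the number trained per session), it is 1,820 to 2,730. Recording of the probe must be added. Masked scoring does not undo any influence of the running score on progression itself, and the report should say so.

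**Option B: demote it.** Move sessions-to-criterion out of the Primary Objective, label it an unblinded process measure, and draw no VR versus non-VR conclusion from it. The cost is wording only.

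**In either case,** reconcile the threshold in Computerized script training with that in Primary Objective so that the outcome has one definition, and state in the Statistical Analysis Plan section which measures the assessor blinding covers.

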### **Secondary Objectives**

Secondary outcome on nonverbal cognition is comprised of a test battery measuring EF, short-term/working memory, and attention used in previous studies of PI that investigated the relation between nonverbal cognition and multi-level language processing (Wong & Law, 2022a) and their changes as a result of functional communication therapy (Wong & Law, 2022b). Attention is assessed via sub-tests 1 (map search) and 3 (elevator counting) of the Test of Everyday Attention (Robertson et al., 1994). The former aims to tap sustained and selective visual attention via identifying the target symbol in a map while the latter assesses auditory selective attention via counting the number of target tones in the presence of distractors with different tones. Verbal short-term and working memory will be examined via digit span forward and backward tasks from the Wechsler Adult Intelligent Scale – 4th edition (2008), respectively. EF will be evaluated via the Test of Nonverbal Intelligence-third edition (TONI-3; Brown et al., 1997), and the Wisconsin Card Sorting Test (WCST; Grant & Berg, 1993). TONI-3 is a norm-referenced test that uses abstract figures to evaluate abstract reasoning and problem-solving. WCST assesses cognitive flexibility and reasoning via matching cards with respect to color, quantity, and shape upon different rules and feedback given.

In accordance with the Research Outcome Measurement in Aphasia (ROMA; Wallace et al., 2018), the aphasia quotient of CAB, and CANELT (Wong et al., 2023), a standardized 6 measure adapted from the Amsterdam-Nijmegen Everyday Language Test (ANELT; Blomert et al., 1994), will be included as secondary outcomes in language and communication, respectively. CAB is a standardized aphasia test for measuring aphasia severity. CANELT assesses verbal communication effectiveness in conversation via 20 culturally appropriate scenarios. PWA's self-reported outcome on communication and quality of life will be examined via the Cantonese version of the 20-item

Communication Outcome after Stroke (Can-COAST) Scale (Kwok & Wong, 2023) translated from its original English version (COAST; Long et al., 2008). All assessment tasks and their sources of normative data (if applicable) are summarized in Table 1.

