### **Statistical Analysis Plan:**

Assessment will be administered by a research postgraduate student with speech therapy background or trained speech therapy students who are blinded to the assignment of treatment condition. Scoring will be done by the research postgraduate student. Data analyses will be carried out by PI and Co-Is. Treatment and generalization probes will be scored by the Naming and Oral Reading for Language in Aphasia 6-point scale (NORLA-6) with some adaptations. NORLA-6 has been validated (Pitts et al., 2018) and adopted in a number of script training studies (e.g., Cherney et al., 2014; 2019). (R2) Adaptations in the current study concern the accuracy judgment of responses that semantically acceptable production will also be considered accurate during scoring. The time for script production will also be calculated. For secondary outcomes, PWA's performance on various cognitive tasks and CANELT will be transformed into z-scores. A principal component analysis will be carried out to group tests that share similar cognitive components. Linear mixed effect (LME) models will be used to investigate the research questions with timepoint and experimental conditions as fixed variables and different primary/secondary outcomes as predicted variables. Any significant results will be followed by post-hoc comparisons. Variables that may interfere with the outcomes such as age, aphasia severity, and education, will be included and controlled in the model.

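### The nonverbal cognition outcome takes in digit span, which the protocol itself labels verbal, so a gain confined to verbal memory could be reported as a nonverbal cognitive gain

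*Protocol*

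**What the plan says.** The protocol's Research Questions draw a line between verbal and nonverbal effects. Question 2 concerns the nonverbal side alone: "Can script training enhance nonverbal cognitive functions of Cantonese-speaking PWA". Question 3 names both sides: "Can VR magnify verbal and nonverbal treatment outcomes of script training of PWA".

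The Secondary Objectives then define the outcome meant to answer the nonverbal questions: "Secondary outcome on nonverbal cognition is comprised of a test battery measuring EF, short-term/working memory, and attention". The tests for each domain follow in the same paragraph:

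- Attention: "Attention is assessed via sub-tests 1 (map search) and 3 (elevator counting) of the Test of Everyday Attention".
- Memory: "Verbal short-term and working memory will be examined via digit span forward and backward tasks".
- Executive function: "EF will be evaluated via the Test of Nonverbal Intelligence-third edition", together with the WCST.

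The protocol's Statistical Analysis Plan section standardises the scores ("PWA's performance on various cognitive tasks and CANELT will be transformed into z-scores") and adds: "A principal component analysis will be carried out to group tests that share similar cognitive components". Linear mixed models by timepoint and condition are then fitted to the outcomes.

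**The concern.** The outcome is called nonverbal, yet one of its three domains is measured only by tests that the protocol calls verbal. The verbal/nonverbal boundary is the trial's own, and it is what gives Question 2 a meaning apart from Question 1, which already asks about verbal functional communication.

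The boundary matters in this population. All participants have aphasia, and both active arms consist of repeated spoken practice: reading turns in unison with a virtual therapist, reading them aloud alone, and repeating corrected responses. If verbal memory improved and nothing else did, the protocol's definition would let that improvement count as a benefit to nonverbal cognition. The same holds for the VR versus non-VR comparison in Question 3. This is the only outcome the protocol offers for Question 2, so no second measure would expose the misattribution.

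**Working it through.** The protocol gives no figure on this point, so the check sets its sections side by side.

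**Step 1. Membership of the outcome (Secondary Objectives).**

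| Domain placed under nonverbal cognition | Tests named | Labelled verbal by the protocol? |
|---|---|---|
| Attention | Map search; elevator counting | No |
| Short-term/working memory | Digit span forward; digit span backward | Yes, both |
| Executive function | TONI-3; WCST | No |

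Named tests: 2 + 2 + 2 = 6. Labelled verbal: 2 of 6 tests and 1 of 3 domains. No memory test without the verbal label is named. This is a count of tests, not a weight in any analysis.

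**Step 2. Does the analysis text separate them (Statistical Analysis Plan section)?** It contains three elements that might do so.

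- *Standardisation.* Putting scores on a common scale does not change which construct a test belongs to.
- *Principal component analysis.* Its grouping follows the correlations in the data, and no rule says how a component containing digit span is to be classed. There are two broad cases:
  - Digit span forms its own component. That component is then the memory part of a battery defined as nonverbal, so a gain on it falls under the nonverbal heading.
  - Digit span loads with other tests, for example with elevator counting, which the protocol describes as an auditory task. The component then mixes tests labelled verbal with tests that are not, and a gain on it cannot be assigned to either side.
- *Covariates.* Aphasia severity is listed among variables that may interfere with the outcomes and are to be controlled. That does not alter which tests count as nonverbal, and it is not described as removing a language gain produced by treatment.

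None of the three keeps digit span out of the nonverbal set.

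**Step 3. Consequence for the research questions.** Suppose the true effect is confined to the two digit span tasks and is zero on the other four tests. Under the definition in Step 1, a significant digit span result is a result on the nonverbal cognition outcome. Question 2, or the nonverbal part of Question 3, could then be answered yes although no test outside the verbal label had changed.

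**Step 4. Size.** Putting a number on the distortion needs the treatment effect on digit span, the correlations among the six tests, and the component loadings or other weights. The protocol gives none of these, so no size is derived.

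**The case against.** The strongest reply is that this is only a label. The protocol says the battery comes from earlier work on nonverbal cognition. The principal component analysis may well separate digit span from the other tests, and the source of any gain would then be visible. Training on particular conversational scripts need not carry over to digit span at all, and the protocol does not describe how digit span is given or answered. The outcome is secondary, and the primary treatment probe is untouched.

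Much of this limits the point without removing it. Earlier use of the battery may explain the label, but it does not make tests the protocol calls verbal into nonverbal ones. Separation by the component analysis would depend on the data, and the protocol would still file the separated component under nonverbal cognition. Transfer from script training to digit span is plausible but undocumented, so the point is about what could be reported, not what will happen.

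A reader might also infer several stronger things that the document does not support:

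- *That digit span carries a known share of a nonverbal score.* No equal-weight composite or single nonverbal score is planned, and the protocol does not say how many scores each test contributes. A percentage weight, or a shift worked out from an assumed gain, would describe an analysis that is not in the plan.
- *That a memory component will emerge and be wholly verbal.* Component membership depends on the data.
- *That the component analysis is faulty because it is not tied to the pre-treatment visits.* The protocol does not say which visits feed it. That detail, and the reference values for the z-scores, may properly sit in a separate statistical analysis plan, so their absence here is no error.
- *That CANELT, a verbal communication test, will enter the component analysis.* It is standardised alongside the cognitive tasks, but the text does not say that it joins the grouping.

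A separate analysis plan does not dispose of the main point. Outcome membership is already fixed in the protocol, and fixed inconsistently, so a later document would have to override it.

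**Conclusion.** The point holds as an inconsistency in how a secondary outcome is defined. The nonverbal cognition outcome includes a memory domain measured only by tests the same paragraph labels verbal, the research questions keep verbal and nonverbal effects apart, and no stated rule reconciles the two. A gain confined to verbal memory could therefore be reported as a nonverbal cognitive gain for Question 2 and the nonverbal part of Question 3.

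Its extent by count is one domain of three and two named tests of six. Its effect on an estimate or on a false claim rate cannot be obtained from the document. The conclusion rests on the protocol's own labels alone. It does not assume that script training improves digit span, or that the components will fall out in any particular way. The primary outcome and the other language and communication outcomes are unaffected. The point should be settled before analysis because this is the only outcome that answers Question 2.

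**What to change.** Report digit span forward and backward as a separate verbal memory outcome. Base Question 2 and the nonverbal part of Question 3 only on map search, elevator counting, TONI-3 and WCST. State this membership in the protocol before the principal component analysis is run, so that the data cannot move a test across the boundary.

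A lighter alternative is to rename the six-test outcome cognition, keep it as described, and state in advance that conclusions about nonverbal function will be drawn only from those four tests.

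Neither route needs new tests, visits or participants. Either one does change the definition or naming of a secondary outcome and should be recorded as a protocol change. The real cost is in scope: memory drops out of the nonverbal set, any component analysis confined to that set has four named tests to work with, and no conclusion about nonverbal memory can be drawn.
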